### Treatment allocation

For intervention allocation a randomization list is drawn up using a computerized randomization computer program (Random Allocation Software version 1.0.0). Patients are randomly assigned to either the intervention group, receiving the risk communication intervention in addition to the managed diabetes care or the control group, receiving managed diabetes care only. Approximately two weeks after the first visit, patients are scheduled for either the intervention or control session to the diabetes nurse and dietician. The manager of the DCS, who is not involved in the patients' care, allocates the patient to one of the two groups on the basis of the randomisation list. The flow of the patients will be registered by a medical assistant according to a flow diagram recommended by the CONSORT statement [43]. Participants may withdraw from the study at their own request and without providing reasons. Provided reasons for withdrawal will be registered. Figure 1 shows the design of the study.

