#### Primary outcome measure

Appropriateness of risk perception is the primary outcome measure. Risk perception will be measured by using a question from a questionnaire previously developed for the IMPALA study [46]. This question is 'If the mean risk of developing CVD in the next 10 years for men with diabetes is 20 of 100 men and for women 15 of 100 women, how would you rate your risk of developing CVD in the next 10 years?' In addition, at 2 and 12 weeks only, a population diagram will also be shown in the questionnaire. Patients will be asked to indicate how many of 100 people will develop CVD in the next 10 years.

Appropriateness of risk perception will be assessed by a comparison of the UKPDS score [44] of the patient with the risk perception. Appropriateness is considered as a patient with a high-risk perception while indeed having a high risk, or a patient with a low-risk perception while having a low risk [46]. According to the UKPDS risk engine, a risk of > 30% is considered high risk, a risk between 15 and 30% is an intermediate risk, a risk < 15% is a low risk.

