### Analyses

Comparability between the two groups will be assessed at baseline. On the basis of an intention-to-treat analysis, differences in changes between the intervention and the control group are measured with 95% confidence intervals at 2 and 12 weeks for both primary and secondary outcomes. For dichotomous outcome variables multilevel logistic regression analyses will be used. To calculate differences between continuous variables linear regression analyses will be used. If there are any relevant differences between the groups, we will adjust data for these factors (i.e. age, gender, diabetes duration, level of education and family history regarding T2DM and CVD).

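### The primary model should always include baseline UKPDS risk, which sets the correct answer but is missing from a conditional adjustment list

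*Protocol article*

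**What the plan says.** All places are in the protocol article.

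- **Primary outcome measure.** "Appropriateness of risk perception will be assessed by a comparison of the UKPDS score [44] of the patient with the risk perception". A response is appropriate for "a patient with a high-risk perception while indeed having a high risk, or a patient with a low-risk perception while having a low risk". The UKPDS classes are below 15% (low), 15 to 30% (intermediate) and above 30% (high).
- **Additional measurements.** The examination and blood samples needed for the UKPDS estimate are taken at baseline.
- **Intervention group.** The risk engine uses nine variables: age at diagnosis, diabetes duration, sex, ethnicity, smoking, systolic pressure, HbA1c, total cholesterol and HDL-cholesterol.
- **Analyses.** The contrast is the between-group difference in changes at 2 and 12 weeks, with multilevel logistic regression for dichotomous outcomes. Adjustment follows only if relevant group differences are found, and then "we will adjust data for these factors (i.e. age, gender, diabetes duration, level of education and family history regarding T2DM and CVD".

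**The concern.** UKPDS risk is not an ordinary prognostic factor here. It is one of the two quantities compared to produce the outcome, so it fixes which answer counts as correct. Background reports that patients tend to underestimate their risk. If that tendency dominates, low-risk patients will often match without help, and high-risk patients only if their perception is corrected. The chance of an appropriate answer would then depend strongly on the risk band.

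Two features of the stated rule sit badly with this. The list, introduced by 'i.e.', leaves out UKPDS risk. And whether to adjust at all is decided after looking at the groups. At stake are some precision in the primary comparison and the discretion that a look-then-adjust rule leaves to the analyst.

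**Working it through.** **The plan's own figure.** Sample size gives 84 per group for a 0.5 SD difference at 90% power. Assuming two-sided alpha of 0.05 (not stated): n = 2 × (1.960 + 1.282)² / 0.5² = 84.1. With 30% dropout, 84 / 0.70 = 120. Both figures reproduce, and neither depends on this point.

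**Assumed inputs.** The article gives no band shares and no match rates by band. Assumptions: shares of 40/40/20% (low/intermediate/high), 84 evaluable per arm, and one of two patterns of appropriateness. The match rate in the intermediate band is also assumed, because the article's definition names only high/high and low/low.

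- Steep: control 70/35/15%, intervention 85/60/45% (overall 45% vs 67%).
- Flat: control 50/40/25%, intervention 72/62/47% (overall 41% vs 63%).

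**Share of outcome variance explained by band (control rates).**

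- Steep: between-band variance = 0.4 × 0.25² + 0.4 × 0.10² + 0.2 × 0.30² = 0.047. Total = 0.45 × 0.55 = 0.2475. R² = 0.19.
- Flat: 0.4 × 0.09² + 0.4 × 0.01² + 0.2 × 0.16² = 0.0084. Total = 0.41 × 0.59 = 0.2419. R² = 0.035.

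**Chance mix, follow-up proportions only.** SD of the arm difference due to band mix = √(2 × between-band variance / 84).

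- Steep: √(2 × 0.047 / 84) = 3.3 points. Flat: √(2 × 0.0084 / 84) = 1.4 points.
- In the steep case this is part of the ordinary standard error, not added to it. The full variance is 2 × 0.2475 / 84 = 0.00589 (SE 7.7 points). Within bands it is 2 × (0.2475 − 0.047) / 84 = 0.00477 (SE 6.9 points). The gap of 0.00112 is 3.3 points squared.

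**Chance mix, difference in changes.** Take baseline rates equal to control rates. Control patients then have zero mean change in every band.

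- Steep: intervention changes are 15, 25 and 30 points, mean 22. Variance across bands = 0.4 × 7² + 0.4 × 3² + 0.2 × 8² = 36, so SD is 6, and 6 / √84 = 0.65 points.
- Flat: every band changes by 22 points, so the SD is 0.
- With no intervention effect and stable rates it is 0 in both patterns.

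**Simulated power, without vs with band.**

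| Primary contrast | Steep | Flat |
|---|---|---|
| Follow-up only | 83% vs 88% | 82.7% vs 83.2% |
| Difference in changes, within-patient correlation 0.4 | 73.0% vs 72.5% | 67.7% vs 67.3% |
| Same, correlation 0.6 | 81.2% vs 80.8% | 76.1% vs 75.6% |
| Same, correlation 0.8 | 91.3% vs 91.1% | 88.6% vs 88.2% |

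On top of baseline appropriateness, adding the band gained roughly 0 to 4 points across these patterns, less as the within-patient correlation rises; one run at correlation 0.4 gave 86.6% vs 89.1%.

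**A stronger assumed association.** A separate logistic simulation (odds ratio 2.5, 84 per arm, Monte Carlo error about 1 point, a few convergence warnings) gave 58% unadjusted, 60% with baseline appropriateness, 62% with a proxy assumed to carry 60% of the risk variance, 67% with the band, and 68% with band and baseline. With no association the band gained nothing (82% vs 80%).

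**Type I error.** Without adjustment it was 4.1 to 5.5% across the scenarios.

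**The case against.** The strongest objection is that the plan states a difference in changes, not a comparison of follow-up proportions. Risk is estimated at baseline, so both answers appear to be scored against the same UKPDS value, and a stable band effect cancels within the patient. This stands for a pure change contrast. It does not settle the matter, because the article does not say how baseline enters a logistic model for a dichotomous outcome. High-risk patients who start wrong also have more room to improve, so change may itself vary by band.

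Second, age, gender and diabetes duration are on the list, and age at diagnosis, sex and duration feed the risk engine. True risk would be partly adjusted for, but only if adjustment is triggered. Smoking, systolic pressure, HbA1c, both cholesterol measures and ethnicity remain off the list.

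Third, the gradient is assumed. Background also reports unrealistically pessimistic patients, and the risk question supplies means of 20 per 100 men and 15 per 100 women, which may pull answers away from low. This stands, and is why the size is given as a range.

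Fourth, covariates are often settled in an analysis plan. Here, however, the article states a rule, and the point is about that rule.

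A reader might infer more: that chance imbalance in true risk biases the primary result, or shifts it by 3.3 points on top of the stated uncertainty. The documents do not support this. Randomisation and the confidence interval already cover chance imbalance, and the 3.3 points belong to a follow-up-only comparison. A reader might also fault the absence of stratification by risk. Treatment allocation says only that "a randomization list is drawn up using a computerized randomization computer program"; silence on strata in a condensed article is not evidence that there are none.

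**Conclusion.** The point holds as an efficiency and prespecification improvement, not as a bias or an error in the sample size. The variable that decides which answer is correct is available at baseline, yet the stated rule omits it and makes all adjustment depend on observed differences.

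Under 40/40/20% shares, 84 per arm and the two patterns used, the power gain is at most about 5 points if follow-up alone is modelled, about 0 to 4 points on top of baseline appropriateness, and about nil for a pure change contrast with a stable band effect. A stronger association than the steep pattern would give more; no association would give none. Because the article supplies neither the shares nor the gradient, precision may be lost, but that it will be lost cannot be asserted.

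**What to change.** In Analyses, state that the primary logistic model for appropriateness at 2 and 12 weeks always includes baseline UKPDS risk (band or percentage, chosen in advance) alongside baseline appropriateness, whatever the observed balance. Show the proportions appropriate by arm within each risk band.

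The cost is a sentence of text and a slightly larger model. UKPDS risk is already needed to score the outcome, so no new data are required and the sample size does not change.

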## Discussion

This article contains an extensive description of the design of the @RISK Study: an intervention to investigate the effects of a newly designed risk communication protocol on risk perception, attitude and intention to change lifestyle behaviour. We expect that due to the risk communication intervention, patients' appropriateness of risk perception will improve in a way that they will understand the meaning of their absolute 10 year risk to develop CVD, and subsequently develop a more positive attitude and intention towards lifestyle behaviour change. Risk communication is very relevant and important for patients with diabetes because nowadays patients are expected to make their own choices and decisions concerning their diabetes care.

Only a few studies on the effectiveness of risk communication on changing patients' risk perception and attitude on lifestyle changes have been performed. Brenner et al. performed a randomised controlled trial on risk communication in patients with hypertension and a CVD risk > 10%. The intervention included educating patients of their 10-year risk of myocardial infarction or death, illustrated by a graphical representation of the risk, and three follow-up phone calls by a physician or study nurse. This resulted in behaviour modification and in a significant reduction in CVD risk [51,52]. A randomised controlled trial by Koelewijn-van Loon et al. found that appropriateness of risk perception improved and anxiety reduced. They found no improvement in lifestyle in patients with high risk of developing CVD. As the risk communication was part of a large intervention study, it is unclear if the risk communication itself has caused the improvement [46,53].

To our knowledge, evidence on this topic for patients with T2DM is scarce and this study might have an important contribution to the research in this field. Only two studies have been performed on patients with T2DM. Asimakopoulou et al. studied the impact of risk communication by means of a combination of visual tools of developing CHD in patients with T2DM. They found that patients improved their risk perception and they were able to recall their risk after six weeks [54]. Edwards et al. evaluated different risk presentation formats in patients with diabetes and showed that patients found graphical representations helpful and had no clear preference for which graphical tool, however it did not change patients' ability to make decisions on their health [18]. These two studies were not based on theory, which makes it difficult to untangle the mechanism of risk perception in relation to self-management. In addition, the purpose of the study of Edwards et al. was to investigate which kind of graphical information was most helpful and not really the risk communication itself.

The key element of this trial is the use of a theoretical framework, based on the Theory of Planned Behaviour [38,39] and the Self-regulation Theory [35-37]. Elements of the intervention are based on the theoretical framework. Communication of absolute risk is based on the illness perception 'cause' of the Self-regulation Theory and the communication by means of a positive message is focused on the 'controllability' of the theory. This message tells patients that they can control their disease themselves.

The population diagram used in this study was already found to be feasible in the IMPALA study [46], which is a trial on the implementation of a nurse-led intervention for cardiovascular risk management in primary care. Their risk communication tool was tested in a pilot study. The risk tool in IMPALA also consisted of a bar chart to explain the possibilities for risk reduction also by relative risk reduction, but process evaluation showed that this was hardly used by the nurses in the IMPALA study.

In this study, much attention is paid to the diabetes nurses' and dieticians' skills to perform the intervention by means of a training program and pilot study. The main strength of this part of the study is the availability of an experienced communication coach who has been performing 'coaching-on-the-job'. This will improve the quality and standardisation of the intervention, rather than supervision in groups, lacking personal feedback to the caregivers.

A limitation of the study design is that we were not able to divide the diabetes nurses and dieticians into two groups: one group that performs the intervention and one group that takes care of the control group. The reason for this limitation is a practical one: we implemented the study into the DCS in which diabetes nurses and dieticians work part-time. If we trained only half of the diabetes nurses and dieticians employed at the DCS, the intervention could not be performed every day of the week. This would cause problems in scheduling the patients, which is likely to influence their willing to participate in the study. Therefore, we decided to train all diabetes nurses and dieticians. To increase treatment fidelity we developed both an intervention and a control group protocol. In addition, we will make tape recordings to assess treatment fidelity.

This study started at the end of 2008 with the training of the diabetes nurses and dieticians, followed by the pilot study. The inclusion of patients started in March 2009 and will continue through February 2010. Results will become available at the end of 2010.

## Abbreviations

CVD: cardiovascular disease; DCS: Diabetes Care System West-Friesland; GP: general practitioner; T2DM: type 2 diabetes mellitus; UKPDS: United Kingdom Prospective Diabetes Study.
